## Abstract

**Background:**

Repetitive transcranial magnetic stimulation (rTMS) is widely used therapy to enhance motor deficit in stroke patients. To date, rTMS protocols used in stroke patients are relatively unified. However, as the pathophysiology of stroke is diverse and individual functional deficits are distinctive, more precise application of rTMS is warranted. Therefore, the objective of this study was to determine the effects of personalized protocols of rTMS therapy based on the functional reserve of each stroke patient in subacute phase.

**Methods:**

This study will recruit 120 patients with stroke in subacute phase suffering from the upper extremity motor impairment, from five different hospitals in Korea. The participants will be allocated into three different study conditions based on the functional reserve of each participant, measured by the results of TMS-induced motor evoked potentials (MEPs), and brain MRI with diffusion tensor imaging (DTI) evaluations. The participants of the intervention-group in the three study conditions will receive different protocols of rTMS intervention, a total of 10 sessions for 2 weeks: high-frequency rTMS on ipsilesional primary motor cortex (M1), high-frequency rTMS on ipsilesional ventral premotor cortex, and high-frequency rTMS on contralesional M1. The participants of the control-group in all three study conditions will receive the same rTMS protocol: low-frequency rTMS on contralesional M1. For outcome measures, the following assessments will be performed at baseline (T0), during-intervention (T1), post-intervention (T2), and follow-up (T3) periods: Fugl-Meyer Assessment (FMA), Box-and-block test, Action Research Arm Test, Jebsen-Taylor hand function test, hand grip strength, Functional Ambulatory Category, fractional anisotropy measured by the DTI, and brain network connectivity obtained from MRI. The primary outcome will be the difference of upper limb function, as measured by FMA from T0 to T2. The secondary outcomes will be the differences of other assessments.

**Discussion:**

This study will determine the effects of applying different protocols of rTMS therapy based on the functional reserve of each patient. In addition, this methodology may prove to be more efficient than conventional rTMS protocols. Therefore, effective personalized application of rTMS to stroke patients can be achieved based on their severity, predicted mechanism of motor recovery, or functional reserves.

**Clinical trial registration:**

https://clinicaltrials.gov/, identifier NCT06270238.

## Introduction

1

### Background and rationale

1.1

Stroke is still worldwide leading cause of disability, and the global burden has been increasing (1, 2). Impairment of upper limb motor function stands out as the foremost and prevalent sequelae of stroke, significantly impacting stroke patients’ independence in activities of daily living (3, 4). Therefore, clinicians are employing various therapies aimed at improving outcomes related to motor function, including conventional rehabilitative physical and occupational therapies.

Transcranial magnetic stimulation (TMS) generates magnetic field to induce electric currents in brain, using a magnetic coil. These currents primarily stimulate axons of the neural circuits and enable to assess motor cortex function or corticospinal connectivity (5). By recording motor evoked potentials (MEPs) in distal muscles following TMS, disease-related changes in corticospinal output can be assessed. Therefore, TMS has been proven useful as a predictor of motor recovery in stroke patients using measures such as motor threshold, amplitude and latency of MEP, cortical silent period, or central motor conduction time (5, 6). Since the early 2000s, the use of repetitive transcranial magnetic stimulation (rTMS) has emerged and is now widely utilized to enhance upper limb function in stroke patients, due to its feasibility, non-invasive nature and painless application (7–10). The underlying patho-mechanisms in applying rTMS therapy was mainly based on the neuroplasticity and the interhemispheric competition model theory (11–14). Applying rTMS to human cortex has been proven to modulate cortical excitability, leading to recovery or reorganization of the functional connectivity (5, 15). The neuroplasticity, in the context of stroke, is thought as the brain’s capacity to modulate its activity in response to stimuli, thereby compensating for damages resulting from stroke (16). rTMS therapy targets this plasticity by either inhibiting or exciting neural activity to induce or restore the desired plasticity in the brain (17, 18). In stroke patients in the acute phase, it is known that along with functional loss in the ipsilesional hemisphere, there are alterations in the interaction between the ipsilesional hemisphere and the contralesional hemisphere via the corpus callosum (19). It is thought that in regions remote from the brain lesion, there may be changes in neuroanatomy and cortical activity in both cerebral hemispheres (20). As a result, bilateral activation of both primary motor cortices is observed during movement in post-stroke patients, resulting in poor motor function compared to healthy people (21). Based on these theories, in stroke patients, many previous studies have demonstrated the effect of inhibitory low-frequency rTMS or continuous theta burst stimulation (cTBS) applied at contralesional primary motor cortex (M1) and facilitatory high-frequency rTMS or intermittent theta burst stimulation (iTBS) applied at ipsilesional M1 in enhancing upper limb function (22, 23).

The currently well-known conventional rTMS protocols for stroke patients involve applying inhibitory rTMS at the contralesional M1 or facilitatory rTMS at the ipsilesional M1. However, some studies demonstrated that these conventional rTMS protocols showed no significant effects when applied to severe hemiplegic stroke patients (24, 25). These results may imply that cortical activity or neural plasticity of individual stroke patients is not unified. Also, in cases where ipsilesional motor pathways are severely damaged, stimulating M1 may not be the optimized therapy for enhancing upper limb motor recovery. In fact, some previous studies have investigated the ipsilesional premotor cortex (PM) or supplementary motor area (SMA), and contralesional PM may replace the function of the damaged ipsilesional M1, although no consensus has been reached yet (26–29). Schulz et al. demonstrated a significant interaction between the corticospinal tract (CST) and corticocortical connections, implying that the ipsilesional ventral PM plays a role in patients with significant damage in CST (30). Sankarasubramanian et al. (31) also reported that the contralesional dorsal PM may support recovery in patients who have experienced extensive damage to ipsilesional motor pathways. In addition, Di Pino et al. (32) suggested a bimodal balance recovery model over the interhemispheric competition model. They suggested that interhemispheric balancing should be considered along with the functional reserve spared by every patient in the recovery model, not in isolation. Given the diverse underlying pathophysiology and recovery processes within stroke, this suggestion appeared reasonable. In 2018, Harvey et al. (33) demonstrated that applying inhibitory rTMS at ipsilesional M1 did not show effectiveness. Following the release of this trial, increasing inquiries have emerged regarding the rationality of applying conventional rTMS protocols based on the interhemispheric competition model. Ultimately, it is believed that employing a conventional rTMS approach, which applies the same protocol to everyone without considering individual characteristics, has limitations. Therefore, a consideration of individual functional reserve will be necessary for the implementation of rTMS tailored to each individual.

Besides the stimulating target of rTMS, another important consideration when applying rTMS therapy is the accuracy of the stimulation. The conventional rTMS treatment approach has historically positioned the area of maximal magnitude of the electric field induced by TMS along the central axis of the stimulation coil. Stimulation was conducted by aligning the coil to ensure that the central axis of the coil passed through the stimulation area. Additionally, determining the stimulation area was achieved by identifying the location that elicited the largest transcranial magnetic stimulation-induced motor-evoked potentials (TMS-induced MEPs), requiring numerous attempts of TMS to accurately ascertain the stimulation site (34). In addition, protocols based on anatomical landmarks or the 10–20 system have been used to stimulate non-motor areas where TMS-induced MEPs are not measured, which may increase the imprecision of rTMS targeting (35). Recently, a neuronavigation system is considered a viable method for obtaining accurate stimulation targets. However, a critical limitation of employing the neuronavigation is its expense, making it difficult to utilize in general environments (36). Recent advancements in neuroimaging techniques have enabled the development of computational brain modeling and electric field simulation techniques based on brain images such as magnetic resonance imaging (MRI) obtained from patients, which can address the limitations of conventional rTMS targeting methods (37, 38). Specifically, through the prediction and analysis of electric fields reflecting the unique anatomical information of the patient’s brain based on MRI, it has been revealed that the area of maximum magnitude of the electric field does not necessarily align with the central axis of the coil due to variations in brain structure (39, 40). Moreover, simulations have shown that when stimulating areas are targeted to achieve maximum field strength, actual TMS-induced MEPs are increased (41). Therefore, it is imperative to utilize electric field simulations and optimization processes based on brain imaging obtained from patients to determine the position and orientation of the TMS coil that will generate the optimal stimulation for the given target stimulation area. This approach should be applied to rTMS therapy to ensure its effectiveness.

Therefore, the aim of this study is to demonstrate the efficacy of rTMS protocols based on the functional reserve of individual stroke patients, including exploring the accurate stimulating target. We anticipate that our study protocols will demonstrate superiority over the conventional inhibitory rTMS protocol applied to the contralesional M1. Additionally, by utilizing the MRI of each individual patient, we aim to achieve accurate stimulation targets without relying on the neuronavigation, thereby offering convenience and cost-effectiveness for broader use. In addition, we would like to explore the mechanisms of personalized rTMS by performing serial resting-state functional MRI (rs-fMRI) and diffusion tensor imaging (DTI).

## Methods and analysis

2

### Study setting

2.1

This is a prospective, single-blind with blind observer, parallel-group design, multi-center, randomized controlled clinical trial. This study will recruit 120 patients with stroke in the subacute phase who are suffering from the upper extremity motor impairment, from five different hospitals in Korea. Participating hospitals are Samsung Medical Center, Seoul; Seoul National University Hospital, Seoul; Bucheon St. Mary’s Hospital, The Catholic University of Korea, Seoul; St. Vincent’s Hospital, The Catholic University of Korea, Seoul; Yongin Severance Hospital, Yongin.

The participants will be allocated into three different study conditions according to their functional reserve, as follows: Study condition (1) participants with preserved ipsilesional CST, confirmed by response of TMS-induced MEPs, Study condition (2) participants with no response of TMS-induced MEPs, but with preserved ipsilesional PM cortex and ipsilesional CST confirmed by DTI, and Study condition (3) participants with no preservation of ipsilesional CST. After the allocation, participants will be randomly assigned to the intervention-group or control-group of each study condition through randomization. The participants of the intervention-group in the three study conditions will receive different protocols of rTMS intervention: Study condition (1) high-frequency rTMS on ipsilesional M1, Study condition (2) high-frequency rTMS on ipsilesional ventral PM, and Study condition (3) high-frequency rTMS on contralesional M1. The participants of the control-group in all three study conditions will receive the same rTMS protocol: low-frequency rTMS on contralesional M1. A schematic diagram is shown in Figure 1.

**Figure 1 fig1:**
[figure not shown]
Design and flowchart of the study.

Evaluations to assess the functional reserve and motor function will be conducted as follows: (1) at baseline (T0), (2) after 1 week, following 5 sessions of rTMS intervention [during-intervention (T1)], (3) at the end of the rTMS intervention [post-intervention (T2)], and (4) 2 months after the end of the intervention [follow-up (T3)]. The specific timeline of participants is shown in Table 1.

**Table 1 tab1:** Timeline of enrolment, interventions, and assessments of this study.

	Enrolment	Baseline	Intervention (1 ~ 5)	During-intervention	Intervention (6 ~ 10)	Post-intervention	Follow-up
*Timepoint*		*T0*		*T1*		*T2*	*T3*
Informed consent	O						
Eligibility screen	O						
Allocation		O					
Assessments							
rs-fMRI		O				O	O
DTI		O				O	O
T1-MRI		O				O	O
TMS-induced MEPs		O		O		O	O
FMA		O		O		O	O
Box and block test		O		O		O	O
ARAT		O		O		O	O
Jebsen-Taylor hand function test		O		O		O	O
Hand grip strength test		O		O		O	O
FAC		O		O		O	O
Adverse events			O	O	O	O	O
Application of intervention							
Intervention			O		O		

rs-fMRI, resting-state functional MRI; T1-MRI, T1-weighted structural images of brain MRI; TMS-induced MEPs, transcranial magnetic stimulation induced motor evoked potentials; FMA, Fugl-Meyer Assessment; ARAT, Action Research Arm Test; FAC, Functional Ambulation Category.

### Eligibility criteria

2.2

The inclusion criteria for this study are as follows: (1) hemiplegic stroke (ischemic or hemorrhagic stroke with corresponding lesion determined by MRI or computed tomography scan) patients in the subacute phase (7 days to 3 months from the onset) who are currently hospitalized, (2) Fugl-Meyer Assessment (FMA) score of the upper extremity ≤42, (3) adequate language and cognitive function to perform at least a 1-step obey-command, (4) pre-stroke functional level of modified Rankin Scale (mRS) ≤1, (5) aged ≥19 years old, and (6) patients willing to sign the informed consent. The exclusion criteria are as follows: (1) patients with transient ischemic attack, defined as a rapid-onset focal neurological deficit lasting less than 24 h (42) (2) those with contraindications to rTMS, such as epilepsy, implanted metal objects in the head, or a history of craniotomy, (3) those with progressive of hemodynamically unstable medical conditions, (4) those with coexisting neurological conditions, such as spinal cord injury or Parkinson’s disease, (5) those with major psychiatric disorders, such as major depression, schizophrenia, or dementia, (6) those having contraindications to conduct an MRI study, (7) those who are pregnant or lactating, and (8) patients who have refused to participate in this study.

### Allocation

2.3

The 120 eligible participants will be allocated into three study conditions based on the functional reserve of each participant, measured by the results of the brain MRI, TMS-induced MEPs, and DTI evaluations. Each condition will consist of 40 patients and they will be randomly allocated into the intervention-group and control-group in a 1:1 ratio. The allocation will be performed by the one researcher of each participating hospital, who will be responsible for the randomization, will not have contact with the participant, and will not be involved in data collection or analysis. The randomization will be done by using a randomization table generated by the www.randomization.com. The randomization sequence will be concealed and only the research principal investigator (PI) will have access authority.

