### Sample size, recruitment

3.4

Based on the primary outcome of this study and previous literature, we have established the study’s power (1-β) at 80% and a significance level (α) of 5%. The clinically significant effect size (δ) has been designated as 7.25, with an expected standard deviation (σ) of 7.70 (67, 68). Sample size calculation was conducted using Lehr’s formula, with an expected follow-up rate of 90% (68, 69). Finally, the calculated sample size was 120, with each subgroup consisting of 40 participants.

Recruitment of the study participants will be conducted by each participating hospital.

Every research investigator will recruit participants from each hospital who are eligible to participate in the study. Participants will be informed about the current treatment guidelines regarding upper extremity dysfunction in stroke patients, as well as the potential and adverse effects of this study.

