### Data management and monitoring

3.6

All data will be collected using standardized electronic Case Report Form (eCRF) and study participants will be identified only by a research-specific serial number. All personal information and collected data of participants will be maintained in confidentiality under the responsibility of research PI of each participating hospital. All personal information and collected data of participants will be maintained in confidentiality under the responsibility of the research PI of each participating hospital. They will be stored in password-protected files and kept in a locked facility. Routine supervision of the data will be conducted by one of researchers in each participating hospital, independent of other research investigators. Data analysis will be conducted by data analysts, independent of other research investigators. PIs will meet every month to review the implementation of this study. There are no conflicts of interest among all participating researchers.

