## Ethics and dissemination

The PI of the Samsung Medical Center will be the Chief Investigator (CI) of this study. The CI will inform the other PIs of each participating hospital regarding important protocol amendments. The CI will report these amendments to the Ministry of Food and Drug Safety of the Republic of Korea. The PI of each participating hospital will report these amendments to their respective ethics committee and research teams.

Prior to inclusion of participants, all participating hospitals obtained institutional review board (IRB) approval for this study (Samsung Medical Center, 2023–11-164; Seoul National University Hospital, 2,312–167-1498; Bucheon St. Mary’s Hospital and St. Vincent’s Hospital, The Catholic University of Korea, XC24DND30004; Yongin Severance Hospital, 9–2024-0013). If any protocol modifications are needed, further approval from the IRB will be obtained from all participating hospitals. Informed consent will be obtained from all participants prior to their inclusion in this study by research investigators. In addition, this study has been registered in the clinicaltrials.gov (NCT06270238). The results of this study are expected to be published within 2 years of its completion.

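### Section 2.3 gives access to the randomisation sequence only to the research PI, an investigator at a recruiting hospital, so allocation concealment is not secured as written

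*Protocol article*

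**What the plan says.** Four statements in section 2.3 (Allocation) of the protocol article matter here.

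- Source of the list: "The randomization will be done by using a randomization table generated by the www.randomization.com".
- Who uses it: "The allocation will be performed by the one researcher of each participating hospital, who will be responsible for the randomization".
- That researcher's independence: he or she "will not have contact with the participant, and will not be involved in data collection or analysis".
- Who may see it: "The randomization sequence will be concealed and only the research principal investigator (PI) will have access authority".

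On enrolment, section 3.4 says: "Every research investigator will recruit participants from each hospital who are eligible to participate in the study". Ethics and dissemination adds: "Informed consent will be obtained from all participants prior to their inclusion in this study by research investigators".

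The title research PI is not tied to one person. Section 3.6 uses it for the lead at every site, with personal information and collected data held "under the responsibility of the research PI of each participating hospital". Ethics and dissemination makes the PI of one participating hospital the Chief Investigator and refers to separate PIs at the others.

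**The concern.** Allocation concealment means that nobody who decides whether and when a patient enters the trial can foresee the next assignment. The plan already has a suitable holder for the list: a researcher at each site, kept away from participants, data collection and analysis. The access sentence gives the list to the PI instead and, by the word *only*, to no one else.

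The PI belongs to the investigator side, which recruits and takes consent. Someone who can read a pre-generated list can hold back or bring forward a patient according to the next assignment. Any imbalance in prognosis that results exists before treatment starts, so blinded assessment of the Fugl-Meyer upper-limb score cannot remove it. This is a rule that the article states, so it differs from a detail that an article may leave to the full protocol.

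**Working it through.** The point turns on who has which role, so the main check sets the statements side by side.

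**1. Who can see upcoming assignments?** Section 2.3: the research PI only. The list is a pre-generated table, so access to it is access to future assignments.

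**2. Who is that PI?** There are two readings.
- Each site PI (the usage in section 3.6): five holders, one at each of the five recruiting hospitals.
- The Chief Investigator: one holder, who is the PI of one of those five hospitals (Ethics and dissemination).

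On both readings the holder is an investigator at a hospital that recruits. On the second, direct exposure may be confined to one site in five.

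**3. Who enrols?** Section 3.4: every research investigator. Ethics and dissemination: research investigators take consent. Neither statement exempts the PI, and neither names the PI.

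**4. Is there a barrier elsewhere?** The article does not bar the PI from recruiting, consenting or assigning the study condition. It mentions no central release of assignments and no sealed envelopes.

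**5. Does the independent researcher supply the barrier?** Only if that person controls the list. Under the access sentence the researcher carries out assignments from a list that the PI can read. The researcher's distance from participants then does not stop the PI from knowing what comes next.

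**6. The plan's own figure.** Inputs from section 3.4: difference 7.25, SD 7.70, Lehr's formula, 90% follow-up.
- n per arm = 16 / (7.25 / 7.70)² = 18.05, taken as 18.
- 18 / 0.9 = 20 per arm, so 2 × 20 = 40 per condition and 3 × 40 = 120 in total.

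The stated 120 is reproduced. It does not decide the point. It supplies the arm size of 20 for the next step, and none of its inputs depends on who holds the sequence.

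**7. Illustration of size.** Two inputs are assumptions without a source in the document: k = 4 patients in one condition with better prognosis, and g = 5 points of extra expected gain each.
- Even split (2 and 2): contribution to the arm difference = (2 − 2) × 5 / 20 = 0.
- All four in one arm: (4 − 0) × 5 / 20 = 1.0 point.
- Relative to the planned difference: 1.0 / 7.25 = 14%.

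The shift is linear in both inputs. Halving either gives 0.5 point (0.5 / 7.25 = 7%), and doubling either gives 2.0 points (2.0 / 7.25 = 28%). With no steering it is zero. The shift does not depend on whether there is a true treatment effect.

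**The case against.** The strongest reply is that the two sentences of section 2.3 can coexist. The PI may be custodian of the list and release assignments, while the site researcher applies them one by one without seeing the rest. The article also says that the sequence will be concealed, and the authors may have had only custodial or emergency access in mind. This stands against a reader who infers a flat contradiction: the text is ambiguous about how the two roles fit. It does not help with foreknowledge, because a custodian PI can still read ahead.

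Secondly, no statement names the PI as a recruiter. That is correct. The inference rests on the wording of section 3.4 that every research investigator recruits, and on the absence of any exemption.

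Thirdly, Table 1 places consent and eligibility screening before allocation, and the study condition rests on motor evoked potential and DTI findings. Both limit the room for steering. Neither prevents someone who knows the list from timing an enrolment.

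A reader might go further in two directions that the document does not support.
- *The PI judges eligibility and withdrawals.* No statement says who judges eligibility. Section 2.5 leaves withdrawals for other reasons to the researchers in general. The meeting in section 3.6 ("PIs will meet every month to review the implementation of this study") concerns implementation and says nothing about enrolment decisions.
- *Blinding through the analysis is broken.* Section 2.4 promises blinding of participants, assessors and data analysts. PI access by itself breaks none of these, and section 3.6 makes the analysts independent of the other investigators.

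**Conclusion.** The point holds in a limited form. The stated access rule allows an investigator at a recruiting hospital to know upcoming assignments, and the article contains nothing that keeps that person out of recruitment, consent or assignment of the study condition. Concealment is therefore asserted but not secured.

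It would be too strong to say that concealment has failed. No breach is shown, PI recruitment is inferred, and the number of sites exposed depends on which PI is meant.

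The size is unknown. The 1.0-point shift (14% of 7.25) shows only what modest steering could do under assumed inputs, and it is no estimate for this trial. The point is a cheap improvement to a basic safeguard.

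**What to change.** Replace the last sentence of section 2.3 with wording to this effect: the sequence is accessible only to the independent allocating researcher at each hospital (or to one central holder who takes no part in recruitment); each assignment is released after consent, eligibility and study condition have been recorded; no PI or recruiting investigator has access to the sequence during recruitment.

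If the authors meant the PI to have emergency access only, the section should say so and limit that access to the single participant concerned.

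The cost is a change of wording and of access rights. The independent researchers are already in the plan. Sample size, power and significance level stay as they are.
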